**5.7. Does the study involve the use of deception and/or incomplete disclosure?**

☐ No ☒ **Yes:** *If yes, explain the use of deception/incomplete disclosure and describe why it is necessary to achieve the goals of the study.*

Participants will be told to use the mock online retail space to choose a beverage for their child, and that the beverage will either be sent to them for free or they will receive \$5. At the end of the study, we will debrief participants on the study purpose and inform them that all participants receive \$5. This very minor deception enables us to incentivize participants to behave as they normally would when shopping online and to minimize potential social desirability bias introduced by participating in a study.

**5.8. When all research-related study procedures are complete, are there plans for long-term follow up?**

☒ No ☐ **Yes:** *If yes, indicate what data will be collected during this period.*

**5.9. Does the study involve the collection of specimens (e.g. blood, cells, tissues, fluids, secretions, recombinant or synthetic nucleic acids, biological toxins, bacteria, virus, fungi, etc.)**

☒ No ☐ **Yes:** *If yes, indicate the [COMS Registration Number](#) or plans to obtain COMS approval.*

**5.10. Does the study involve the use of existing data, documents, records, and/or specimens for secondary analysis?**

☒ No ☐ **Yes:** *If yes, indicate how, when, where, and from whom data, documents, records, and/or specimens will be obtained.*

**5.11. Are there provisions for medical and/or psychological support resources available to participants (e.g., in the event of incidental findings, research-related stress)?**

☒ No ☐ **Yes:** *If yes, describe the provisions and their availability.*

**5.12. Describe the data and safety monitoring plan for the study. This plan should outline how study progress will be monitored throughout the lifecycle of the research to ensure the safety of subjects, as well as the integrity and confidentiality of data.**

Although the survey distribution company will need to collect email addresses to send the \$5 incentives to participants, they will remove the email addresses from the dataset before delivering it to us. All data will be delivered to the researchers de-identified with no identifiers other than IP addresses. Confidentiality of data will be ensured by solely keeping data on [name] password-protected work laptop.

**5.13. Are there any anticipated circumstances under which participants will be withdrawn from the research without their consent?**

☒ No ☐ **Yes:** *If yes, describe the circumstances for withdrawal as well any associated procedures to ensure orderly termination, appropriate referrals, and/or follow-up care.*

6. **Recruitment Methods** ☐ N/A. *Skip to next section.*

*Upload recruitment materials to the “Local-Site Documents” page in ESTR.*

6.1. **Indicate how, when, where, and by whom participants will be recruited.**

**Provide a list of materials used to recruit participants, e.g., emails, posters, and/or scripts here.**

We will use [Qualtrics](#), a leading research firm that recruits research participants through their online panels and other online communities, social networks, and websites, to recruit participants with the following eligibility criteria: 1) primary caregiver of a child 0-5 years old; 2)  $\geq 18$  years old; and 3) U.S. citizen. For our study, participants will be sent an invitation asking them to “take a survey” to avoid selection bias based on survey topic.

7. **Consent Process**

*Upload consent form(s) and debriefing materials, if applicable, to the “Local-Site Documents” page in ESTR.*

7.1. **Describe how the research team will invite participants to take part in the research and obtain consent to participate. If the research team will not obtain informed consent, provide justification for requesting a waiver or alteration of consent (and/or parental permission).**

Qualtrics will invite participants to take part in the research by sending an invitation asking them to “take a survey”. Before conducting the survey, they will be directed to an informed consent page (See **Appendix A**).

7.2. **Describe how the research team will document the consent process (e.g., participant/researcher will both sign and date the consent document; participants will thumbprint the consent document; electronic consent will be obtained and associated with the participant’s research record). If the research team will not obtain signature and date, provide justification for requesting a waiver or alteration of documentation of consent (and/or parental permission).**

Participants will check “yes” to indicate that they have read the informed consent language and wish to proceed to the survey. As the researchers will receive de-identified survey results, we will not obtain a signature and date. The survey will not advance forward if they do not provide informed consent. Participants will be given the option of checking “no” and refusing to take part in the study at any time.

7.3. **Will participants be offered a copy of the consent information?**

☒ Yes ☐ No: *If no, explain why not.*

7.4. **If consent will be obtained in a language other than English, identify the language(s) that consent information will be provided, who will be responsible for translation, and the provisions for communicating this information to participants.** ☒ N/A

7.5. **If the research involves deception and/or incomplete disclosure, describe the debriefing process. Explain when participants will be debriefed, who will debrief them, and how they will be debriefed.** ☐ N/A

Participants will receive a debriefing form at the end of the survey explaining the small deception, and they will have the opportunity to check a box if they wish to exclude their data from use in our study (see **Appendix A**).

7.6. **If the research involves secondary use of existing data, documents, records, and/or specimens, and the research team will not obtain consent, describe how consent was originally obtained. Additionally, either upload the original consent form to the ESTR record or confirm that the original consent process obtained participants’ permission to share or use their data/specimens for future research projects.** ☒ N/A

8. **HIPAA Privacy Protections** ☒ N/A. *Skip to next section.*

*HIPAA applies to US-based research involving the collection or use of protected health information (PHI) from a hospital, health center (including the Harvard Dental Center), health plan, or health insurance plan (i.e. a covered entity). The Privacy Rule will not directly regulate researchers who are engaged in research within organizations that are not covered entities even though they may gather, generate, access, and share personal health information (PHI). The Privacy Rule applies only to individually identifiable health information held or maintained by a covered entity. Individually identifiable health information that is held by anyone other than a covered entity, including an independent researcher who is not a covered entity, is not protected by the Privacy Rule and may be used or disclosed without regard to the Privacy Rule.*

- 299 8.1. Explain how the Privacy Rule applies to this specific research project.
- 300
- 301 8.2. Describe the covered entity involved in this research that holds or maintains the PHI that will be used by the
- 302 researchers.
- 303
- 304 8.3. Describe plans for obtaining authorization to access protected health information or provide the rationale for a
- 305 waiver of authorization.
- 306
- 307

308 9. Research Subject to the European Union (EU) General Data Protection Regulation (GDPR) ☒ N/A. Skip to next section.

309 *GDPR applies to research involving the collection of “personal data” from research subjects who are located in the EEA. This*

310 *includes biospecimens. The EU/EEA includes the 28 states of the European Union (Austria, Belgium, Bulgaria, Croatia, Republic*

311 *of Cyprus, Czech Republic, Denmark, Estonia, Finland, France, Germany, Greece, Hungary, Ireland, Italy, Latvia, Lithuania,*

312 *Luxembourg, Malta, Netherlands, Poland, Portugal, Romania, Slovakia, Slovenia, Spain, Sweden, & United Kingdom) and four*

313 *additional countries: Iceland, Liechtenstein, Norway and Switzerland.*

314

- 315 9.1. Describe plans to collect and/or obtain “pseudonymized data” (e.g., coded data) and/or identifiable data and/or
- 316 biospecimens from participants in the EEA.
- 317
- 318

319 10. Research Subject to the Family Educational Rights and Privacy Act (FERPA)

320 ☒ N/A. Skip to next section.

321 *FERPA applies to research involving the collection of individually identifiable information from student records or personal*

322 *education information from an education program (defined as: any program principally engaged in the provision of education,*

323 *including, but not limited to, early childhood education, elementary and secondary education, postsecondary education, special*

324 *education, job training, career and technical education, and adult education).*

325

- 326 10.1. Describe plans to collect and/or obtain individually identifiable information from student records or personal
- 327 education information from an education program.
- 328
- 329

330 11. Vulnerable Populations ☒ N/A. Skip to next section.

- 331 11.1. Identify all vulnerable populations (e.g., children; pregnant women, human fetuses, neonates; prisoners; elderly;
- 332 economically disadvantaged; employees or students of the investigator or sponsor; undocumented individuals;
- 333 refugees; racial and/or ethnic minorities; illiterate or low-literacy; military personnel; terminally ill; cognitively
- 334 impaired or mentally ill; persons with a stigmatizing disease or condition, e.g. AIDS/HIV, etc.) and describe
- 335 safeguards to protect their rights and welfare.
- 336
- 337

338 12. Risks

339 *Risks may be physical, psychological, social, legal, reputational, and/or financial.*

340

- 341 12.1. Describe the reasonably foreseeable risks, discomforts, and/or inconveniences to participants and/or the
- 342 group/community to which they may belong. Indicate the probability, magnitude, and duration of each risk.
- 343

344 There is a very small risk of breach of data confidentiality, but we expect such a breach would impose no more than

345 minimal risk to study participants. The study involves a very minor deception that enables us to incentivize participants to

346 behave as they normally would when shopping online and to minimize potential social desirability bias introduced by

347 participating in a study. While this may cause brief discomfort to some participants, they were told that they would either

348 receive a drink or \$5, so the fact that they receive \$5 should not come with too much discomfort.

349

- 350 12.2. Identify whether any of the information collected, if disclosed outside of the research, could reasonably place the
- 351 participant at risk of criminal or civil liability or be damaging to the participant’s financial standing, employability,
- 352 insurability, or reputation.
- 353

354 None of the information collected would place participants at risk of the above.

355

- 356 12.3. Outline provisions in place to minimize each risk identified above.
- 357

358 No identifiable information besides IP addresses will be delivered to the research team by the survey distribution company.

359 After study completion, IP addresses will be stripped from the dataset so that responses cannot be linked up with this

information. Survey responses will be downloaded from the Qualtrics website and stored on a secure drive. Only the researchers involved in this study will have access to the data.

### 13. Benefits

#### 13.1. Describe the potential benefits to individual participants, if any, and/or society. If there are no direct benefits, state that here. Note: payment/compensation is not a benefit.

There are no direct benefits to participants. For society, results of this work are timely and can directly inform federal regulation of claims and imagery on food and beverage packaging. The FDA is currently considering changes to claims and other FOP labeling as a part of its Nutrition Innovation Strategy, which aims to reduce preventable death and disease related to poor nutrition, in part by empowering consumers to make better, more informed decisions. The FDA is particularly interested in exploring science-based modifications to claims related to added sugars, especially on products that contain fruit. However, the agency lacks supporting data on how different FOP claims and marketing influence consumers' beverage perceptions and purchase intentions. We have discussed our research intentions with several FDA Senior Advisors for Nutrition Policy, and they have expressed strong support and interest in our work.

### 14. Participant Privacy

#### 14.1. Describe provisions to protect participants' privacy (their ability to control and limit the extent, timing, and circumstances of sharing information about themselves with others, e.g., the use of a private interview room) and to minimize any sense of intrusiveness that may be caused by study questions or procedures.

Qualtrics will need to collect email addresses from some participants if they wish to receive the extra \$5 incentive. These email addresses will solely be used by Qualtrics to send the \$5 to participants and then will be destroyed by the survey company. The survey results that Qualtrics will send us will have no identifiable information besides IP addresses. IP addresses are recorded to ensure data quality—duplicate responses from identical IP addresses indicate an individual may have taken the survey twice, and duplicate responses will be removed from the dataset. After study completion, IP addresses will be stripped from the dataset so that responses cannot be linked up with this information. Survey responses will be downloaded from the Qualtrics website and stored on a secure drive. Only the researchers involved in this study will have access to the data.

### 15. Data Confidentiality

#### 15.1. Indicate the [identifiability](#) of the data/specimens:

☐ Data/specimens will not contain any direct or indirect identifiers (anonymous data).

☒ Data/specimens will contain direct or indirect identifiers, but the research team will remove them upon receipt (de-identified data).

☐ Data/specimens will contain indirect identifiers (i.e., number, letter, symbol, or combination thereof) and the research team will maintain a key that links identifiers to individual participants (coded data).

☐ Data/specimens will contain direct identifiers (identifiable data).

☐ None of the above; describe:

#### 15.2. Have any identifiable data/specimens been de-identified for use in this research study?

☐ No ☒ Yes: *If yes, describe how you will prevent any re-identification.*

Qualtrics will need to collect email addresses from some participants if they wish to receive the extra \$5 incentive. These email addresses will solely be used by Qualtrics to send the \$5 to participants and then will be destroyed by the survey company. The survey results that Qualtrics will send us will have no identifiable information besides IP addresses. IP addresses are recorded to ensure data quality—duplicate responses from identical IP addresses indicate an individual may have taken the survey twice, and duplicate responses will be removed from the dataset. After study completion, IP addresses will be stripped from the dataset so that responses cannot be linked up with this information.

#### 15.3. Identify where data/specimens will be stored (e.g., on campus at Harvard or remotely, in a specimen laboratory) and describe the provisions to maintain confidentiality (e.g., password protection, encryption, locked filing cabinets, etc.). Refer to the [Investigator Manual](#) and the [Harvard Research Data Security Policy](#) for additional information.

Data will be stored on a Harvard password-protected laptop on the Harvard Chan server in a password-protected folder.

#### 15.4. Indicate whether any data/specimens will be transferred/transmitted and describe the plan to share the data/specimens (e.g., outside of Harvard, to other researchers, to collaborators). Indicate who may request access and how. If data/specimens will be transferred/transmitted/shared, describe how, when, and to whom.

No data will be transmitted or shared with others.

**15.5. Indicate whether participants' permission will be obtained to share their data/specimens and/or use their data/specimens in other future research projects.**

No data from this study will be used for future research projects.

**15.6. Indicate who is responsible for data/specimen management and how the research team and/or other collaborators are permitted access to information.**

[name] is responsible for data management. The survey is de-identified and no identifiable information besides IP addresses will be given to the researchers from Qualtrics. Survey responses will be downloaded from the Qualtrics website and stored on a secure drive. Only the researchers involved in this study will have access to the data. [name] will be the primary holder of the data, and if [name] needs access to it, she will share it via a secure file transfer system.

**15.7. Indicate how long data/specimens will be stored and describe the plans at the end of the storage period (e.g., are data/specimens destroyed, returned to data/specimen provider, etc.).**

De-identified survey results will be stored on a secure server and destroyed 7 years after publication.

**16. Data/Statistical Analyses Plan**

**16.1. Describe plans for analysis (including the statistical method, if applicable).**

Linear regression will be used to examine mean total calories and grams of added sugar purchased between our experimental groups. Logistic regression will be used to compare proportions in each condition that chose different beverage types. Because of the randomized design, the only covariates we will control for will be purchasing frequency (for secondary outcomes), and those that may by chance significantly differ among the groups. A Bonferroni-Holm correction will be used to control for multiple comparisons. In secondary analyses we will stratify the main effects by SNAP/WIC status, race/ethnicity, household income, and frequency of child fruit drink consumption.

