**5.6. Describe study procedures.**

After providing informed consent, participants will complete a 10-15 minute survey. They will be asked to answer all questions based on their oldest child 0-5 years old, and will provide the age of the child. First, participants will be told to use a mock online retail store to choose a beverage for their child that will be sent to them (or they will receive \$5). In reality, at the end of the study, we will debrief participants on the study purpose and inform them that instead of receiving the beverage they selected, all participants will be compensated with \$5 through the survey distribution company (twice the value of a typical beverage in the store). This very minor deception enables us to incentivize participants to behave as they normally would when shopping online and to minimize potential social desirability bias introduced by participating in a study. Participants will then be shown images of 12 different beverages (random order) consisting of commonly purchased beverages in various categories, with oversampling for fruit drinks (e.g., 6 fruit drinks, 1 milk, 2 100% juices, 2 regular sodas, and 1 water). The variety will provide a realistic shopping scenario for generalizability. Participants will be required

to click on beverages to see an enlarged package before choosing. After selecting their beverage, participants will advance in the survey to view four randomly ordered fruit drinks one at a time and answer questions about their health knowledge, product beliefs, and purchase intentions. See **Appendix A** for full survey (consent + debriefing language) and **Appendix B** for images.

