**Label Randomization.** Caregivers will be randomized using simple randomization via the Qualtrics platform to see fruit drinks in our online store and survey with one of the following seven label conditions (**Appendix B**). The first condition (*claim & imagery*, control) will represent the status quo and contain a 100% Vitamin C claim and fruit imagery. Conditions 2-4 will involve the removal of package elements for fruit drinks high in added sugar (“high sugar”,  $\geq 10\text{g/serving}$ , 20% DV): Condition 2 (*imagery only*) will have fruit imagery but no 100% Vitamin C claim on high-sugar fruit drinks; Condition 3 (*claim only*) will have a 100% Vitamin C claim but no fruit imagery on high-sugar fruit drinks; and Condition 4 (*no claim or imagery*) will feature no imagery or claims on high-sugar fruit drinks. Conditions 5-7 will involve the addition of package elements. Condition 5 (*imagery, claim, & text % fruit juice disclosure*) will show a text description of the percent fruit juice in each fruit drink, to see if it changes the effects of the claim and imagery. The sixth (*imagery, claim, & added sugar warning*) and seventh conditions (*imagery, claim, & added sugar warning w/teaspoons of sugar*) will test the effects of added sugar warnings.

**Primary Outcomes:** The primary outcomes will be total calories and grams of added sugar purchased in the online store task (averaged by condition). We will also examine the percentage of people in each condition that purchased a drink high in added sugars ( $>20\%$  DV) for their child, and the percentages that chose each category of drink (fruit drinks, 100% juice, etc).

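### On the survey order described in 5.6, purchasing frequency and child fruit drink frequency appear to be reported after label exposure, yet 16.1 uses them as covariate and stratifier without restriction to pre-exposure variables

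*Protocol*

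**What the plan says.** Section 5.6 gives the sequence. After consent and the child's age, "First, participants will be told to use a mock online retail store to choose a beverage for their child". Then, "After selecting their beverage, participants will advance in the survey to view four randomly ordered fruit drinks one at a time", with questions on knowledge, beliefs and intentions about them. Participants are randomised "to see fruit drinks in our online store and survey with one of the following seven label conditions", so the assigned label is present in both parts. Section 5.6 names no item on buying or drinking habits and refers the reader to Appendix A "for full survey (consent + debriefing language) and" to Appendix B for the images.

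Section 16.1 uses two habit items. It says that "the only covariates we will control for will be purchasing frequency (for secondary outcomes", "and those that may by chance significantly differ among the groups". It adds that in secondary analyses "we will stratify the main effects by SNAP/WIC status, race/ethnicity, household income, and frequency of child fruit drink consumption". Nothing in 16.1 says when the two frequency items are asked, or requires that a covariate or stratifier be measured before the label is seen.

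**The concern.** A covariate or stratifier in a randomised comparison should be something the allocation cannot have changed. On the described order, a caregiver reports fruit drink habits only after shopping among labelled products and rating four more. A parent who has just read sugar warnings might report less frequent use than one who has just read Vitamin C claims.

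If so, adjusting for purchasing frequency removes part of the label effect on the secondary outcomes, and stratifying on child consumption compares differently selected caregivers across arms. Stratified store outcomes have the further oddity that the stratifier would be reported after the outcome. At stake are the perception results, which are part of the stated aim, and the subgroup results by fruit drink frequency.

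**Working it through.** **Timing.** The child's age is the only participant item that 5.6 names ahead of the store, although the eligibility criteria in 5.5 imply some screening. No habit item is named before the store, and none is named after it. Post-exposure collection is the more natural reading, but it is not stated.

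**Reference size from the plan.** Section 16.2 gives 700 per group, at least 80% power, alpha 0.05 and 18 kcal. No SD is stated, so the figure can only be solved backwards. Two-sided, by normal approximation:

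- Detectable difference = (1.960 + 0.842) × √(2/700) = 0.150 SD.
- Implied SD = 18 / 0.1498 = 120.2 kcal. As a check, an SD of 120 kcal needs 698 per group.

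The plan's figure is therefore attainable. The argument below needs only the 0.150 SD.

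**Bias from adjustment.** Let the label lower reported frequency by d (in SD), and let r be the within-arm correlation of reported frequency with a standardised outcome. In a linear model with a common slope, the adjusted label effect differs from the unadjusted one by r × d. It moves toward zero when the label pushes the report and the outcome in directions that agree with their correlation. Both d and r are assumptions, because the protocol gives neither.

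| d (SD) | r | Bias (SD) | Share of 0.150 SD |
|---|---|---|---|
| 0 | any | 0 | 0% |
| 0.1 | 0.3 | 0.03 | 20% |
| 0.3 | 0.5 | 0.15 | 100% |

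**Independent check with milder inputs.** Here true habit relates to reported frequency with correlation 0.7 to 0.9 and to the outcome with coefficient 0.2 to 0.4, and d is 0.05 to 0.2.

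- Smallest bias: 0.2 × 0.7 × 0.05 = 0.007 SD, about 5% of 0.150.
- Largest bias: 0.4 × 0.9 × 0.2 = 0.072 SD, about 48% of 0.150.
- A simulation of 400,000 records at the largest setting gave an unadjusted effect of −0.155 and an adjusted effect of −0.083. The difference of 0.072 agrees with the formula.
- In the same simulation, splitting on reported frequency gave about −0.105 and −0.112 in the two strata, against a true −0.150.
- With d = 0 the formula gives no bias, and simulated adjusted and unadjusted effects agreed to within 0.002.

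**Route into the primary models.** The imbalance rule in 16.1 is not confined to secondary outcomes or to pre-exposure variables. Between two arms of 700, a label-induced shift in reported frequency of 0.05, 0.1 or 0.2 SD would be significant at two-sided 0.05 with probability 0.15, 0.46 or 0.96. A shift caused by the label could then be treated as chance imbalance and adjusted for. These are pairwise figures; 16.1 does not say which test is applied across the seven groups.

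**The case against.** The strongest objection is that the timing is not documented. Appendix A holds the survey and is not shown, and the absence of a habit item before the store in 5.6 is matched by its absence afterwards. That stands, and the point has to be conditional.

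Second, reports of habitual behaviour may not move after a short task, in which case the bias is zero. That also stands, and the range must start at zero. The mechanism is most plausible for the two warning conditions; it is less obvious where package elements are only removed or a juice percentage is added.

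Third, a reader might infer that the trial's label effects in general, including calories and added sugar, are biased. The protocol does not support this. Purchasing frequency is a covariate for secondary outcomes only, and the stratification is secondary. Only the imbalance rule could carry such a variable into the primary models.

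Fourth, asking about drink habits before the store could prime the primary outcome in a design that conceals its topic. Priming that is equal across arms can still alter label effects, so asking later is a defensible choice.

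What remains is that 16.1 commits to using both items with no pre-exposure condition, while the described order makes post-exposure reporting likely.

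**Conclusion.** The concern holds as a conditional one. If the two items are asked after the label has been seen and the label shifts the answers, the adjusted secondary effects and the frequency-stratified effects are biased. The size is 0 to 0.15 SD for assumed shifts of 0 to 0.3 SD and correlations of 0.3 to 0.5. The upper end equals the 0.15 SD detectable with 700 per arm, but it needs the largest shift and the largest correlation together. Neither the timing nor a shift is established by the protocol, so it would be wrong to say that bias has been shown. The unadjusted, unstratified primary comparisons are not directly affected.

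**What to change.** In 16.1:

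- Limit covariates and stratifiers to variables measured before the store task or that the label cannot change, and apply the same limit to anything added under the significant-imbalance rule.
- State when the two frequency items are asked. If Appendix A already places them before the store, one sentence settles the matter.
- Otherwise, make the secondary-outcome models without purchasing frequency the main analysis. Tabulate reported child fruit drink frequency by arm, and report those strata as exploratory.

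The cost is some precision in the secondary models. With the assumed correlations of 0.3 to 0.5, dropping the covariate widens standard errors by a factor of 1/√(1 − 0.09) = 1.05 to 1/√(1 − 0.25) = 1.15. Randomisation keeps the unadjusted comparison valid. Moving the items ahead of the store is optional, because of the possible priming of the primary outcome.
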